| Statistical Analysis | 
Data obtained from the study subjects will be analyzed in three forms; safety set, Intention to Treat (ITT) set, and Per Protocol (PP) set. Descriptive statistics will be used to define baseline characteristics, Mean and SD will be used to report AEs
 
Seroconversion rates will be compared using the chi-square test with Yates correction or the Fisher's exact test
 
Serum vibriocidal titers will be reported using Geometric mean titers (GMT) and Geometric mean fold rise (GMFR). A p-value of less than 0.05 will be considered the threshold to claim statistical significance.
                                                                                                                                                                                                                                                                                                                                                                                                                                                                                                                                                                                                                                                                                                                                                                                                                                                                                                                                                                                                                                                                     |

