##### Secondary:

- To evaluate and compare the safety of Euvichol-Plus with Shanchol in healthy adults and children.

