**Safety endpoints:**

- Solicited adverse events (Day 0 ~ 3) and Unsolicited adverse events (Day 0 ~ 28) including abnormal vital signs and physical examination.
- SAE (Day 0 ~ 28) including abnormal vital signs and physical examination.

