**Systemic Reactions (Protocol specific)**

- All reaction during the study will be inquired & recorded for up to 30 minutes on the day of each vaccination and for 3 days post-vaccination. Systemic reactions (fever, Headache, acute allergic reaction, Loss of Appetite, fatigue, vomiting and diarrhea) will be recorded.
- Solicited reactions will be graded as follows.

| General reaction | Mild (Grade 1)                                    | Moderate (Grade 2)                                                                 | Severe (Grade 3)                                                   | Potentially Life Threatening (Grade 4)     |
|-------------------------|----------------------------------------------------------|-------------------------------------------------------------------------------------------|---------------------------------------------------------------------------|---------------------------------------------------|
| Fever                   | 38.0-38.4°C                                              | 38.5-38.9°C                                                                               | 39 – 40                                                                   | > 40.0°C                                          |
| Headache                | No interference with activity                            | Repeated use of non- narcotic pain reliever > 24 hours or some interference with activity | Significant; any use of narcotic pain reliever or prevents daily activity | Emergency room (ER) visit or hospitalization      |
| Fatigue                 | No interference with activity                            | Some interference with activity                                                           | Significant; prevents daily activity                                      | ER visit or hospitalization                       |
| Myalgia                 | No interference with activity                            | Some interference with activity                                                           | Significant; prevents daily activity                                      | ER visit or hospitalization                       |

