| Vomiting/ Nausea        | No interference with activity or 1 – 2 episodes/24 hours | Some interference with activity or > 2 episodes/24 hours                                  | Prevents daily activity, requires outpatient IV hydration                 | ER visit or hospitalization for hypotensive shock |

| General reaction | Mild (Grade 1)                    | Moderate (Grade 2)              | Severe (Grade 3)                                                          | Potentially Life Threatening (Grade 4) |
|-------------------------|------------------------------------------|----------------------------------------|----------------------------------------------------------------------------------|-----------------------------------------------|
| Diarrhea                | 2 – 3 loose stools or < 400 gms/24 hours | 4 – 5 stools or 400 – 800 gms/24 hours | 6 or more watery stools or > 800gms/24 hours or requires outpatient IV hydration | ER visit or hospitalization                   |

The occurrence of solicited systemic reactions will be noted in subject diary card by the parent/LAR and copied on to relevant section of the CRF pages by the investigator/designee at the subsequent clinic visit. These reactions will be recorded on the “Solicited Systemic Reactions” section of the CRF along with ‘Date of resolution’; if they do not resolve satisfactorily by 3 days following study immunization.

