#### Unsolicited Adverse Events

An unsolicited adverse event is an observed adverse event that follows immunization but does not fulfill the conditions prelisted in the patient diary in terms of symptom/sign and/or timing of onset post-vaccination. All such events will be recorded in the ‘Adverse event’ pages in the CRF.

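### The synopsis plans to report adverse events by mean and SD, which does not show how many subjects were affected; separately, the solicited-reaction lists and severity scales disagree

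*Supplement*

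**What the plan says.** The Statistical Analysis entry of the Protocol Summary (3.0) gives one method for adverse events: "Mean and SD will be used to report AEs". It does not say what is averaged. Section 12.0 defines the safety set as subjects given at least one dose and sets a 0.05 significance threshold. It contains no adverse-event summary that would override the synopsis.

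The secondary objective (4.7) is comparative: "To evaluate and compare the safety of Euvichol-Plus with Shanchol in healthy adults and children". The safety endpoints (4.8) are SAEs and "Solicited adverse events (Day 0 ~ 3) and Unsolicited adverse events (Day 0 ~ 28) including abnormal vital signs and physical examination".

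Under Systemic Reactions in section 10.2, the text names the reactions to be captured: "fever, Headache, acute allergic reaction, Loss of Appetite, fatigue, vomiting and diarrhea) will be recorded". The next bullet says that solicited reactions "will be graded as follows" and introduces a table with rows for fever, headache, fatigue, myalgia, "Vomiting/ Nausea" and diarrhea, each with four grades. Section 10.3 asks for mild, moderate or severe for every solicited reaction and every unsolicited event. The Unsolicited Adverse Events paragraph defines an unsolicited event as one that "does not fulfill the conditions prelisted in the patient diary in terms of symptom/sign and/or timing of onset post-vaccination".

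**The concern.** A safety comparison needs the number of subjects in each arm who had an event. A mean and SD do not report that. If events are counted, one subject with many events weighs the same as many subjects with one. If subjects are scored 0 or 1, the SD carries no information beyond the proportion. This is a stated method that does not suit the endpoint, so it is more than detail left to a later analysis plan.

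The mismatch between the lists is a separate matter, and it affects what is counted. Solicited and unsolicited events are separate endpoints, and the boundary between them is what the diary prelists. Section 4.5 names nausea/vomiting and myalgia among the most frequent reactions to Euvichol-Plus in the first 7 days, so two of the terms in question can be expected to occur.

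**Working it through.** The plan gives no safety figure to reproduce, so the check has three parts.

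**1. What mean and SD convey.** Input: 208 subjects per arm (section 6.2). The two arms below are constructed examples, not forecasts.

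- Arm X: 20 subjects with 1 event each. Total 20 events; mean = 20/208 = 0.096. SD = √[(20 − 208 × 0.09615²)/207] = 0.296. Incidence = 20/208 = 9.6%.
- Arm Y: 4 subjects with 5 events each. Total 20 events; mean = 20/208 = 0.096. SD = √[(4 × 25 − 208 × 0.09615²)/207] = 0.688. Incidence = 4/208 = 1.9%.

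The means are identical and incidence differs fivefold. The SDs differ, but a reader cannot recover the number of affected subjects from mean and SD.

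For a 0/1 indicator with proportion p, SD = √[p(1 − p)]. At p = 3.4% this is √(0.034 × 0.966) = 0.181. At p = 10% it is √(0.10 × 0.90) = 0.300. The SD is fixed by p and adds nothing.

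The protocol itself reports earlier safety data as subjects and percent. The section 4.5 figures reproduce: 102/2,999 = 3.40%, 69/2,999 = 2.30%, 35/2,999 = 1.17%. A mean event count could not be set beside them.

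**2. The two lists in section 10.2.**

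| Term | Named in the text | Row in grading table |
|---|---|---|
| Fever | yes | yes |
| Headache | yes | yes |
| Fatigue | yes | yes |
| Vomiting | yes | yes |
| Diarrhea | yes | yes |
| Acute allergic reaction | yes | no |
| Loss of appetite | yes | no |
| Myalgia | no | yes |
| Nausea | no | yes (joined with vomiting) |

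Five of nine terms agree; two appear only in the text and two only in the table. They cannot easily be read as two lists kept apart on purpose, because the paragraph after the table sends solicited systemic reactions to a single diary card and a single CRF section.

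**3. The severity scales.** The section 10.2 table has four grades, the fourth being potentially life-threatening. Section 10.3 has three levels and expressly covers solicited reactions. Nothing says how a grade 4 reaction is entered on the three-level scale.

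**The case against.** Several points on the other side stand.

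- A reader might infer that mean and SD allow no valid interval for the arm difference. That is not so. For a 0/1 indicator the mean is the proportion, and at p = 3.4% the approximate half-width is 1.96 × 0.181 × √(2/208), about 3.5 percentage points. A mean count also supports an interval, but for a different question. The approximation does fail when an arm has no events, since mean and SD are then both zero.
- It is tempting to note that 0.034 − 0.181 is negative and to set this against an exact interval. That compares spread with uncertainty. Like for like, 0.034 ± 1.96 × 0.181/√208 gives 0.9% to 5.9%, close to the exact 1.4% to 6.8% for 7 of 208. The 3.40% itself counts drug reactions over 7 days in subjects aged 1 to 40, whereas this trial solicits over Day 0 to 3 after each dose at ages 1 to 60. It serves only as an illustration here.
- Acute allergic reaction and loss of appetite might seem to have no grade. Section 10.3 gives them a generic severity; what they lack is a row of their own.
- Abdominal pain, a known event for both vaccines in section 4.5, is on neither list. No passage requires every known reaction to be solicited, and it would be captured as unsolicited. Adding it would be a preference.
- The diary and annexure are not shown, so it cannot be said that the diary is ambiguous. No event is lost either way, because anything not prelisted goes to the adverse-event pages of the CRF.
- No separate analysis plan is shown, so missing table layouts or tests are not counted here.

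None of this removes the explicit mean and SD sentence or the conflict between the passages.

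**Conclusion.** The point holds in two limited parts. First, the stated summary does not suit event-type endpoints: followed literally, it would not report how many subjects were affected, and a fivefold difference in incidence could sit behind equal means. Second, the solicited terms differ by two in each direction and the severity scales differ by one level, so the classification of four terms depends on which list the diary carries.

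A reader might conclude that the safety comparison cannot be interpreted at all. The documents do not support that. Subject-level events, severity and relatedness are recorded and the safety set is defined, so incidence by arm can be tabulated without new data. Safety is a secondary objective, and the primary immunogenicity conclusion is untouched. How far the solicited rate would move cannot be stated, because the diary is not available and the protocol gives no expected rates for the four terms under its own Day 0 to 3 definition.

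**What to change.** Replace the synopsis sentence, and carry the replacement into section 12.0, with wording such as: the number and percentage of subjects with at least one solicited adverse event, unsolicited adverse event and SAE will be presented by arm and age cohort on the safety set, with exact 95% confidence intervals and the between-arm risk difference with its 95% confidence interval. Exact intervals remain informative with no events: the upper limit is 1 − 0.025^(1/208) = 1.8% for an arm and 1 − 0.025^(1/104) = 3.5% for an arm within one age cohort.

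Reconcile the section 10.2 text, the section 10.2 table and section 10.3 into one solicited list and one severity scale, and use them unchanged in the diary, the CRF and the table. Which terms and scale to keep is for the sponsor to decide.

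The summary is a wording change and can be made at any time before analysis. The list costs a few diary and CRF lines and should be settled before enrolment, because a symptom that was not prelisted cannot be solicited afterwards. If diaries are already in use, the report should state which list they carried and classify events accordingly.

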#### **Cohort 2 children:**

Test: 104 subjects

Reference: 104 subjects

Total Sample size with 10% Dropout is 416. As per published clinical study evaluating immunogenicity of Shanchol and Euvichol, the seroconversion rates (4-fold rise in antibody titres) 14 days after first and second dose of vaccine ranges from 73% to 90% in adults and children. Assuming seroconversion rate of 70% in the reference arm, power of 90%, alpha of 5% (2-sided) and a non-inferiority margin of 10%, 186 subjects would be required in the test and reference arms to establish non-inferiority of the vaccine.

Considering a dropout rate of 10%, a total of 416 subjects will be enrolled in the study (208 in Test and 208 in reference arms).

Approximately 208 subjects enrolled in the study will be adults ( $\geq 18$  to 60 years of age) while remaining 208 would be children ( $\geq 1$  to  $<18$  years of age).

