### **12.0 STATISTICAL METHODS**

Data obtained from the study subjects will be analyzed in three forms; safety set, Intention to Treat (ITT) set, and Per Protocol (PP) set.

The safety set includes all subjects who participated in the study and had at least one dose of the Investigational product, based on which safety will be assessed. The ITT set includes subjects who had at least one measurement of anti-V. Cholera O1 Ogawa, Inaba and O139 antibody titer after investigational product dosing, based on which immunogenicity will be assessed. The PP set includes ITT subjects who completed this study per protocol, based on which immunogenicity will be assessed additionally.

A p-value of less than 0.05 will be considered the threshold to claim statistical significance.

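### The trial is sized for non-inferiority with a 10-point margin, but the only test named for seroconversion is an equality test at p<0.05, which cannot test that margin

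*Supplement*

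**What the plan says.** - **Sizing (section 6.2, repeated in the Protocol Summary).** The reference rate is fixed first: "Assuming seroconversion rate of 70% in the reference arm". With 90% power and two-sided 5% alpha, the text continues: "a non-inferiority margin of 10%, 186 subjects would be required in the test and reference arms to establish non-inferiority of the vaccine". A 10% dropout allowance brings this to 208 per arm, 416 in total.
- **Endpoint (section 4.8).** The primary endpoint is the proportion of subjects with at least a four-fold rise in O1 Ogawa and Inaba titre.
- **Test (Protocol Summary, Statistical Analysis row).** "Seroconversion rates will be compared using the chi-square test with Yates correction", with Fisher's exact test as the alternative.
- **Decision rule (same row and section 12.0).** "A p-value of less than 0.05 will be considered the threshold to claim statistical significance".

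Section 12.0 defines the safety, ITT and PP sets and repeats the p-value threshold. It names no test. The margin appears in neither analysis passage. Confidence intervals appear only as an entry in the list of abbreviations.

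**The concern.** A Yates-corrected chi-square test and Fisher's exact test both address the null hypothesis that the two seroconversion rates are equal. Non-inferiority needs a different null: that Euvichol-Plus is at least 10 points worse. Failing to reject equality is not evidence against that null. Rejecting equality may mean that Euvichol-Plus is better or that it is worse.

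This is described as a pivotal Phase III study and is meant to support licensure in India. If its report follows the analysis text literally, the p-value does not answer the question the trial was sized for. Because the trial is open label, the success rule should be in writing before any results are seen.

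**Working it through.** **Inputs.** From section 6.2: margin 10 points, reference rate 70%, power 90%, two-sided alpha 5% (2.5% one-sided for non-inferiority), 186 evaluable and 208 enrolled per arm. From section 6.4: 1:1 allocation. The test-arm rate is not stated, so it is varied below.

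**Step 1. Is 186 a non-inferiority figure?** The usual formula per arm is

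n = (z₀.₉₇₅ + z₀.₉₀)² × [pT(1−pT) + pR(1−pR)] / (margin + pT − pR)².

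- With pT = pR = 0.70: 10.507 × 0.42 / 0.10² = 441.3, so 442. This does not match.
- With pT = 0.75 and pR = 0.70: 10.507 × (0.1875 + 0.21) / 0.15² = 185.6, so 186. This matches.
- Equality formulas give 477 (70% v 60%) or 392 (70% v 80%), or 496 and 412 with continuity correction. None matches.

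So 186 is reproduced by a non-inferiority calculation at one-sided 2.5%, if a test-arm rate of 75% was assumed. Dropout: 186 / 0.9 = 206.7, so 207, in line with 208.

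**Step 2. One possible result with 186 per arm.** Take 112/186 (60.2%) on Euvichol-Plus and 130/186 (69.9%) on Shanchol.

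- Yates: 372 × (|112×56 − 74×130| − 186)² / (186 × 186 × 242 × 130) = 372 × 3162² / 1,088,390,160 = 3.42. This is below 3.84, and p = 0.0645. Fisher p = 0.0643.
- Difference: −18/186 = −9.7 points. Standard error: √[(0.6022×0.3978 + 0.6989×0.3011)/186] = 4.92 points. 95% interval (Wald): −19.3 to −0.04 points.

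The equality test is not significant, yet the interval runs to nearly twice the margin. With 130 seroconverters on Shanchol, the two rules disagree for every count from 128 down to 111 on Euvichol-Plus. Each of those results is non-significant on the Yates test, and each has a lower 95% limit below −10 points.

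**Step 3. Error rates and power.** Every possible pair of counts was enumerated with exact binomial probabilities, with Shanchol at 70%. The confidence-interval rule is: Newcombe lower 95% limit above −10 points.

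| True Euvichol-Plus rate | n per arm | Yates not significant | Yates significant, Euvichol-Plus better | Interval rule met |
|---|---|---|---|---|
| 58% | 186 | 36.5% | 0.0% | 0.9% |
| 60% (at the margin) | 186 | 51.7% | 0.0% | 2.6% |
| 60% (at the margin) | 208 | 47.0% | 0.0% | 2.6% |
| 70% | 186 | 96.2% | 1.9% | 56.6% |
| 75% | 186 | 83.9% | 16.0% | 90.3% |
| 75% | 208 | 82.2% | 17.8% | 93.1% |

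A Wald interval gives nearly the same results at 186 per arm: 2.5% at 60% and 90.1% at 75%.

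**Step 4. Two readings of the p-value.**

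- If non-significance is taken as success, the false-success rate at the margin is 51.7% at 186 per arm and 47.0% at 208, against a nominal 2.5%.
- If p<0.05 in favour of Euvichol-Plus is required, false success at the margin is essentially nil. The chance of success at 75% v 70% falls to 16.0%, so the planned 90% power is lost.

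**The case against.** The strongest reply has four parts.

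1. **No SAP is shown.** The interval method and formal hypotheses are often left to that document, so their absence alone would be no finding. That is right. But the protocol does name a test, and the test does not fit its own stated aim. An SAP with the correct rule would have to depart from the protocol.
2. **Nothing labels the test as primary, and the margin and alpha are fixed in section 6.2.** A statistician could infer the usual interval comparison from the same counts. The first half stands: the protocol only says how seroconversion rates will be compared, and the sentence also covers the secondary O139 endpoint. But it is the only test given for the primary endpoint, and the only threshold given is p<0.05. The comparison with the margin has to be supplied by the reader.
3. **The 51.7% depends on reading non-significance as success, which the protocol never says.** This stands, so both readings are shown above. The stated test fails under each, in opposite directions.
4. **The Yates correction is a side issue.** This largely stands. At 60% v 70% with 186 per arm, the uncorrected chi-square is non-significant in 47.5% of trials, against 51.7% with the correction. The fault is the null hypothesis, not the correction.

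**Conclusion.** The concern holds. The current text sizes the trial to show non-inferiority within 10 points and then names a test of equality with a p<0.05 threshold. That test cannot establish non-inferiority whichever way the p-value is read.

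The size of the problem depends on the reading. At 186 per arm it is either a false-success rate of about 52% at the margin, or a chance of success of 16% where 90% was intended. These figures assume a 70% Shanchol rate as in section 6.2. The 16% and 90% also assume a 75% Euvichol-Plus rate, which is inferred from the sample size and not stated. The mismatch itself rests on none of these assumptions.

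**What to change.** Replace the test in the Protocol Summary and add the same text to section 12.0:

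- The null hypothesis for seroconversion is pT − pR ≤ −10 points, where T is Euvichol-Plus and R is Shanchol.
- The difference is estimated with a two-sided 95% confidence interval, by one method named in advance (Miettinen-Nurminen or Newcombe).
- Non-inferiority is concluded only if the lower limit is above −10 points.
- The Yates or Fisher equality test is no longer the analysis of the primary endpoint, and the p<0.05 threshold applies to secondary comparisons only.

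The same text should say which analysis set leads and how the Ogawa and Inaba results combine, since the rule cannot be applied without both.

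The cost is a few lines of protocol or SAP wording, with no extra subjects, visits or samples for this change. It does bring a separate point into view: at 186 per arm the correct rule has 90.3% power only if Euvichol-Plus seroconverts at 75%, and 56.6% if both vaccines are at 70%. The assumed test-arm rate should be stated and justified.
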